**Sample labeling**

The labels will be of a quality that remains intact under all temperatures needed in the study. Before taking any sample, correct tubes and accessories shall be checked, and the tubes labeled accordingly. A label will contain ID number and a letter from alphabet to indicate the pre and post treatment follow up time points.

**Sample storage**

-Plasma samples will be stored at -20 oC

-Stool samples will be stored at room temperature (formalin preservation), -20 oC (fresh stool for

PCR)

-Freezer temperature will be recorded regularly with thermometer.

**Sample transport**

Plasma, and stools will be transported to Jakarta on dry ice that will be flown into Flores via Bali or Jakarta.

**Time frame**

The study has a level of funding that was cut down considerably by the grant giving body. The aim was originally, when grant was written to conduct the study for a period of 3 years. However, financial constrains could lead to the earlier termination of the study. In addition, if the results from one and two year interim analysis indicate that it is not ethical to withhold albendazole to half of the study population, the trial will be ended.

**Ethical issues and approval**

The study will be submitted to the Committee of the Medical Research Ethics of the Faculty of Medicine of the University of Indonesia and to the LUMC Committee of Medical Ethics. Further, efforts will be made to ensure approval of the local village leaders and parents/guardians of the study children. To ensure ethical conduct of the trial, all the clinical investigators will follow courses on trial methods (ErasmusMC, Netherlands), courses on GCP and GLP organized by EU funded projects GLOFAL and COINFECT.

**Informed Consent Process**

The principles of informed consent in the current edition of the Declaration of Helsinki will be implemented before any protocol-specified procedures or interventions are carried out. Information will be given in both oral and written form whenever possible. Independent witnesses will be required to attest that illiterate parents/guardians of potential participants have understood the contents of the informed consent.

It is expected that there will be extensive contact between the study team and the populations involved that should lead to the development of mutual trust and the establishment of an ongoing informed consent process attempting to address issues related to interventional studies in resource-limited settings. Many discussions with local community leaders, heads of families and citizens through group meetings, and more limited group interviews will be undertaken prior to trial start.

All relevant information on the possible risks such as discomfort and pain during blood sampling, the acceptance of health workers at monthly intervals they need to honor etc, will be explained. In all cases, the investigator will give the participants ample opportunity to inquire about the details of the trial and to ask any questions before dating and signing the consent forms. Informed consent approved by the ethics committee, will be signed or thumb-printed and dated by the participant’s parent/guardian and by the person who conducted the informed consent discussion. Thumb printing will be used for illiterate persons only

**Appendix 1**

**The forms to record fever and additional malaria-like symptoms**

Date of Visit: ___ ___ . ___ ___ . ___ ___ ___ ___

Name of Subject: _________________________________ Subject ID: ___ ___ ___ ___

Village: ___ Household: ___ ___ ___ Name of Cadre: _______________

1. **Was subject ill since last visit ?** ⁮ Yes ⁮ No

1a. **Symptoms:**

⁮ Fever (including Chills and Sweating)

⁮ Headache

⁮ Fatigue (including Myalgia and Arthralgia)

⁮ Vomiting

⁮ other (specify): _________________

1b. **How long ago ?** _____ days ago / ⁮ currently ill?

1c. **Duration of symptoms** : _____ days

1d. **Temperature (if fever or history of fever):** _________ °C

2. **Did subject take treatment for illness ?** ⁮ Yes ⁮ No

2a. **Who gave treatment ?** ⁮ self-medication ⁮ puskesmas ⁮ doctor ⁮ other

2b. **Name of drug (incl. traditional herbs)**: ___________________________________________

3. **Did subject visit health care center since last visit ?**  ⁮ Yes ⁮ No

3a. **Which ?** ⁮ puskesmas ⁮ doctor ⁮ hospital ⁮ other

3b. **Date of visit:** ___ ___ . ___ ___ . ___ ___ ___ ___

3c. **hospitalized?** ⁮ Yes ⁮ No

4. **Notes:**

|  |
| --- |

**Appendix 2**

**Sample Size Calculation for ImmunoSPIN project**

Calculation are based on data from pilot study and from literature.

*For all calculations power is set at 0.90 and significance level at 0.05*

SKIN PRICK TEST

The 4th column gives the number of people needed in either treatment arm to find a post treatment SPT prevalence as predicted in column 2. In column 5 the number of individuals in either treatment arm needed, presuming that 20% of the people may be lost to follow up (LTFU). The last column gives the total number of enrolments before randomization under this condition.

| Prevalence (P0)  -control group- | Predicted prevalence (P1)  - treatment group- | RR | N = treated | If 20% LTFU | Total enrolments (before randomization) |
| --- | --- | --- | --- | --- | --- |
| **HDM 15%** | 17.5% | 1.2 | 4567 | 5720 | 11440 |
|  | 20% | 1.3 | 1212 | 1515 | 3030 |
|  | **22.5%** | **1.5** | **567** | **709** | **1418** |
|  | **25%** | **1.7** | **334** | **418** | **835** |
|  | 27.5% | 1.8 | 223 | 279 | 558 |
|  | 30% | 2 | 161 | 242 | 484 |
|  |  |  |  |  |  |
| **Cockr. 35%** | 37.5% | 1.07 | 7771 | 9714 | 19428 |
|  | 40% | 1.14 | 1969 | 2461 | 4922 |
|  | 42.5% | 1.21 | 885 | 1106 | 2212 |
|  | **45%** | **1.29** | **502** | **628** | **1256** |
|  | **47.5%** | **1.36** | **324** | **405** | **810** |
|  | 50% | 1.43 | 226 | 283 | 566 |

MALARIAL PARASITEMIA

| Prevalence (P0)  -control group- | Predicted prevalence (P1)  - treatment group- | RR | N = treated | If 20% LTFU,  Treatm. failure | Total enrolments (before randomization) |
| --- | --- | --- | --- | --- | --- |
| **20%** | 17.5% | 0.88 | 5122 | 6403 | 12805 |
|  | **15%** | **0.75** | **1212** | **1515** | **3030** |
|  | **14%** | **0.70** | **822** | **1028** | **2056** |
|  | 12.5% | 0.63 | 507 | 634 | 1268 |
|  | 10% | 0.5 | 266 | 333 | 666 |
|  |  |  |  |  |  |
| **10%** | 7.5% | 0.75 | 2684 | 3355 | 6710 |
|  | 6.75% | 0.67 | 1525 | 1906 | 3812 |
|  | **6%** | **0.60** | **965** | **1206** | **2412** |
|  | 12.5% | 1.25 | 3356 | 4206 | 8412 |
|  | 13.75% | 1.38 | 1562 | 1953 | 3906 |
|  | **15%** | **1.5** | **918** | **1148** | **2295** |

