**Trial design**

Household-based cluster-randomized, double-blind, placebo-controlled trial. Household clustering will be used in order to maximally interrupt the transmission of helminths.

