**Randomization and blinding**

The houses will be marked by Global Positioning System (GPS) system to allow maps to be generated using ARC GIS 9 software (ESRI, USA). Individual’s geographical coordinates will be assigned as well as centre coordinates for households. Computer-aided block randomization by household, using Random Allocation Software will be used to assign treatment groups. The treatment will be coded as A or B and the code will be concealed from investigators and patients. Labels with the study subject ID will be printed from a computer database and attached to the appropriate strip of treatment by the study team located in Jakarta without the involvement of the field study investigators.

A number of nested studies will be conducted which will also use the Random Allocation software to apply to the treatment A and B arms and generate within each of these arms, sub samples for cellular immunological study. The treatment code will be de-blinded when all data needed for analyses are entered into the database.

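### Appendix 2 computes its 90% power for individually randomised people, although the trial randomises households; no allowance for clustering is made

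*Protocol*

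**What the plan says.** The Trial design section describes a "Household-based cluster-randomized, double-blind, placebo-controlled trial", and Randomization and blinding specifies "Computer-aided block randomization by household". The Statistics section refers the sample size wholly to Appendix 2.

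Appendix 2 opens with "For all calculations power is set at 0.90 and significance level at 0.05". It tabulates 12 scenarios for skin prick test (SPT) reactivity and 11 for malarial parasitaemia. The unit is the person: "The 4th column gives the number of people needed in either treatment arm". The only inflation is for 20% loss to follow-up; the malaria column header also names treatment failure. Nowhere does the protocol give a household size, a number of households, an intracluster correlation or a design effect.

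Eight rows are in bold, with total enrolments of 1418, 835, 1256 and 810 for SPT and 3030, 2056, 2412 and 2295 for malaria. None is named as the target.

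**The concern.** When whole households are allocated to one arm, members who resemble each other on the outcome carry less information than the same number of independent people. A calculation for independent people then overstates power. Malaria and SPT reactivity are both primary outcomes, and the Background expects the findings to bear on helminth control policy. A null malaria result would be read against a stated 90% chance of detecting the tabulated difference, and that figure was derived for a different design. A cluster-adjusted analysis would give valid standard errors but would not restore the power claimed at the planning stage.

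**Working it through.** **Inputs from the protocol.** Household randomisation (Trial design; Randomization and blinding). Power 0.90, alpha 0.05, prevalences, N per arm and 20% loss (Appendix 2). Sidedness is not stated.

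**Inputs assumed.** Assessed people per household, m, and ICC. The protocol gives neither.

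**Step 1: reproduce the plan's N.** With p̄ the mean of p0 and p1, the formula for independent subjects is

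n = [1.96·√(2p̄(1−p̄)) + 1.2816·√(p0(1−p0) + p1(1−p1))]² / (p1−p0)²

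Malaria 20% vs 15%: (1.96 × 0.53735 + 1.2816 × 0.53619)² / 0.0025 ≈ 1211.5, against 1212 stated. The bold rows:

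| Outcome | p0 vs p1 | Computed | Stated |
|---|---|---|---|
| House dust mite | 15% vs 22.5% | 567.1 | 567 |
| House dust mite | 15% vs 25% | 334.2 | 334 |
| Cockroach | 35% vs 45% | 502.3 | 502 |
| Cockroach | 35% vs 47.5% | 323.9 | 324 |
| Malaria | 20% vs 15% | 1211.5 | 1212 |
| Malaria | 20% vs 14% | 821.6 | 822 |
| Malaria | 10% vs 6% | 964.6 | 965 |
| Malaria | 10% vs 15% | 917.3 | 918 |

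Of all 23 rows, 22 agree within 3 subjects; the other is 4567 stated against 4573.9 computed. A one-sided test does not fit (988 instead of 1212). Stated N divided by computed N is about 1.00 throughout, so no clustering allowance is hidden in it.

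**Step 2: the loss step.** 1212 / 0.8 = 1515 per arm, and 2 × 1515 = 3030, as stated. After the planned loss, N people per arm remain, with nothing over for clustering.

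**Step 3: add clustering.** Design effect DE = 1 + (m−1)·ICC, and the effective number per arm is N/DE. Power is

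Φ{ [|p1−p0|·√(N/DE) − 1.96·√(2p̄(1−p̄))] / √(p0(1−p0) + p1(1−p1)) }

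Example, malaria 20% vs 15% at DE 1.30: N/DE = 1212/1.30 = 932.3; (0.05 × 30.534 − 1.0532) / 0.5362 = 0.883; power 81%. At a given DE the bold rows all agree to within about half a percentage point:

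| Assumed m, ICC | DE | Power |
|---|---|---|
| 1.5, 0.05 | 1.025 | 89% |
| 3, 0.05 | 1.10 | 87% |
| 2, 0.20 | 1.20 | 84% |
| 4, 0.10 | 1.30 | 81% |
| 4, 0.20 | 1.60 | 73% |
| 5, 0.20 | 1.80 | 68% |

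Malaria is assessed at all enrolled ages, so m of 3 to 5 is illustrated: DE 1.10 to 1.80, power 87% to 68%. SPT is restricted to school-age children, so m of 1.5 to 2 is illustrated: DE about 1.02 to 1.20, power 89% to 84%.

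**Step 4: detectable malaria prevalence at 90% power, DE 1.10 to 1.80.** Against 20% with N = 1212, it moves from 15.0% to between 14.8% and 13.4%. Against 10% with N = 965, it moves from 6.0% to between 5.8% and 4.8%.

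**Step 5: the exception.** House dust mite 15% vs 30% has N = 161, and 161/0.8 is about 202, but the table shows 242 (484 in total). After 20% loss, 242 × 0.8 = 193.6 remain. Power is 94.5% at DE 1.0, 90.1% at 1.2 and 87.7% at 1.3. This row is not bold. Its surplus looks like a slip in the loss step, since no other row has a comparable one.

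**The case against.** The strongest reply concerns malaria. Microscopy is scheduled at seven visits after treatment starts, and the Statistics section commits to methods for longitudinal data, whereas Appendix 2 sizes one comparison of two prevalences. Averaging over visits recovers precision. As an illustration, assume a constant effect, a persistent household correlation and a within-person correlation ρ of 0.3 to 0.5, none of which is in the protocol. The variance factor is then (m−1)·ICC + ρ + (1−ρ)/7. For malaria 20% vs 15% with N = 1212:

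- m = 4, ICC 0.10: factor 0.70 to 0.87, power about 97% to 93%.
- m = 5, ICC 0.20: factor 1.20 to 1.37, power about 84% to 79%.

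This stands as a possibility. It shrinks if the effect builds slowly or the primary comparison is at one visit, and Appendix 2 takes no credit for it. SPT has only two post-treatment assessments.

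Second, the documents do not measure any household correlation. The Trial design section supports household transmission for helminths only, and Appendix 2 does not size that outcome. For malaria and SPT, correlation through shared exposure is likely but assumed. At a design effect of up to about 1.06, power stays within two points of 90%.

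A reader might infer that none of the enrolment figures gives 90% power, or that the trial as designed is underpowered for malaria. The documents support neither. The 484 row keeps 90% up to a design effect of about 1.20, and the power of a longitudinal malaria analysis cannot be computed from what is given.

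**Conclusion.** The stated power is wrong as written: it belongs to an individually randomised design. This conclusion needs no assumption, because it follows from the reproduced N values and the household allocation.

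That every bold row falls below 90% holds for the single-time comparison after the planned 20% loss, given a positive ICC and more than one assessed person per household. The amount rests on assumed m and ICC: about 87% to 68% for malaria and 89% to 84% for SPT. The SPT shortfall may be trivial; the malaria shortfall could be substantial unless the repeated surveys offset it. Whether the trial itself lacks 90% power remains open. What is established is that Appendix 2 does not support the figure it states.

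**What to change.** Revise Appendix 2 as follows.

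1. Apply 1 + (m−1)·ICC separately for malaria (all enrolled ages) and SPT (tested school-age children). Take m from the household census and ICC from pilot or baseline data, and show results over a stated range such as ICC 0.05 to 0.20.
2. State which bold-row enrolment is the target. The bold totals run from 810 to 3030, so there is at present no single enrolment at which to quote power.
3. Restate power, or the detectable prevalence at 90% power, at that enrolment.
4. If precision from the repeated malaria surveys is relied on, include it in the same calculation with its assumed within-person correlation and the assumed course of the effect.
5. Reconcile the 242 and 484 in the house dust mite 15% vs 30% row with N = 161 and 20% loss.

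The cost is a revision of one appendix. It does not require more subjects or any change in allocation. The downside is that the stated power is likely to be less favourable than 0.90.

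### Appendix 2's malaria table treats treatment failure as loss to follow-up (N/0.8), which does not protect the 0.90 power if failures are analysed in their randomised arm

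*Protocol*

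**What the plan says.** Appendix 2 of the protocol sets common parameters for both of its sample-size tables: "power is set at 0.90 and significance level at 0.05". Each table lists a control prevalence P0, a predicted treatment-group prevalence P1, a per-arm N, an inflated per-arm figure and a total.

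For skin prick testing, the text explains the inflated column by loss to follow-up alone: "presuming that 20% of the people may be lost to follow up (LTFU"). For malarial parasitaemia, a primary outcome, the header of the same column adds a second item, treatment failure, beside the same 20% ("Treatm. failure | Total enrolments (before randomization").

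The bold malaria rows, from P1 to total, are:

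- P0 20%: "15% | 0.75 | 1212 | 1515 | 3030"
- P0 20%: "14% | 0.70 | 822 | 1028 | 2056"
- P0 10%: "6% | 0.60 | 965 | 1206 | 2412"
- P0 10%, an increase: "15% | 1.5 | 918 | 1148 | 2295"

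The protocol does not split the 20%, define treatment failure, or say whether P1 already allows for it. It names no analysis population. The section on methods and timing of assessments schedules malaria microscopy before treatment and every 3 months to month 21, and exempts nobody on grounds of treatment failure.

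**The concern.** Loss to follow-up and treatment failure act on power in different ways. A person lost to follow-up contributes no outcome, so enrolling N/(1 − loss) restores the analysed number. A person in whom treatment fails still has blood smears and still belongs to the arm as randomised. That person leaves the sample size intact but pulls the arm's prevalence back towards the control value. Extra enrolment at the rate N/(1 − f) is not enough to offset this, because required N varies roughly with the inverse square of the difference between arms.

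The malaria table names both problems but makes only the correction that suits the first. The skin prick row with the same N of 1212 is also inflated to 1515, so nothing has been added for failure. At stake is whether the malaria totals carry the power attached to them.

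**Working it through.** **Inputs from Appendix 2.** Power 0.90; significance level 0.05 (sidedness not stated, but two-sided reproduces the table); equal arms (total = 2 × per-arm figure); P0, P1, N and inflated N from the bold rows.

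**Inputs assumed.** A share f of the albendazole arm are failures, who stay in the analysis at prevalence P0. P1 describes effectively treated people. The remaining 20% − f of each arm is lost. The protocol gives no value for f, so it is varied from 0 to 20%.

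**Step 1: reproduce the table.** With p̄ = (P0 + P1)/2,

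N = [1.960·√(2p̄(1 − p̄)) + 1.282·√(P0(1 − P0) + P1(1 − P1))]² / (P0 − P1)².

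For 20% versus 15%: (1.0532 + 0.6872)² / 0.0025 = 1211.5, so 1212, as stated. All 11 malaria rows reproduce to within 1 per arm. The inflated column is N/0.8: 1212/0.8 = 1515. Only one row departs from this by more than rounding (4206 against 4195, 0.3%).

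**Step 2: dilute the effect.** P1* = P1 + f(P0 − P1), and the analysed number per arm is 1515 × [1 − (0.20 − f)].

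Example with f = 20%: P1* = 0.15 + 0.20 × 0.05 = 0.16 and analysed n = 1515. Then z = (0.04·√1515 − 1.960·√(2 × 0.18 × 0.82)) / √(0.16 + 0.1344) = (1.557 − 1.065)/0.5426 = 0.907, so power is 0.818.

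**Step 3: results for 20% versus 15%** (stated total 3030). The last column recomputes N at P1* and divides by 1 − (0.20 − f).

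| Failures f | Loss | P1* | Analysed per arm | Power | Total for 0.90 |
|---|---|---|---|---|---|
| 0% | 20% | 15.00% | 1212 | 0.900 | 3030 |
| 5% | 15% | 15.25% | 1288 | 0.886 | 3180 |
| 10% | 10% | 15.50% | 1364 | 0.868 | 3366 |
| 15% | 5% | 15.75% | 1439 | 0.845 | 3592 |
| 20% | 0% | 16.00% | 1515 | 0.818 | 3874 |

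**Step 4: the other bold rows.**

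| Row (stated total) | Power at f = 5% | 10% | 20% | Total for 0.90 at f = 5%, 10%, 20% |
|---|---|---|---|---|
| 20% vs 14% (2056) | 0.886 | 0.867 | 0.816 | 2158, 2288, 2642 |
| 10% vs 6% (2412) | 0.884 | 0.864 | 0.809 | 2546, 2710, 3154 |
| 10% vs 15% (2295) | 0.891 | 0.877 | 0.839 | 2372, 2476, 2770 |

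**Step 5: the usual shortcut.** Dividing N by (1 − loss)(1 − f)² is only approximate. For 20% versus 15% it gives 2 × 1212/(0.9 × 0.81) = 3325 at 10%/10%, against 3366, and 2 × 1212/0.64 = 3788 when all 20% are failures, against 3874. It falls short because the variance terms also change with P1*.

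**The case against.** The strongest reply is that P1 is labelled as the treatment group's prevalence, which is an arm-level figure. Enrolment does not require helminth infection, so P1 is in any case an average over a mixed arm. If failures are already inside it, diluting P1 again counts them twice and power stays at 0.90. This reading is possible and the protocol does not exclude it. But on this reading treatment failure has no place in the inflation column, so the header is wrong instead.

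A second reply is that failures might be left out of the analysis, which would make N/0.8 arithmetically right. The protocol does not say so. Doing it would select on an event after randomisation, and if failure means failure of albendazole it would do so in one arm only. The nominal power would be kept by giving up the randomised comparison.

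Third, Appendix 2 is a grid of scenarios with several bold rows and no single chosen total, and it already shows what a smaller effect costs: 20% failure turns 14% into 15.2%, close to the adjacent bold 15% row. This stands. It means that no particular enrolment total can be called too small, only that the column does not deliver what its header claims.

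Two stronger readings should be resisted. A reader might infer that power is simply below 0.90. The documents do not support that without the three assumptions above, and with 5 points of failure the loss is under 2 percentage points. A reader might also add a full 20% failure to a full 20% loss, which takes the 20% versus 15% row to 0.727. That departs from the table's single 20% covering both.

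**Conclusion.** The point holds in conditional form. The malaria table assigns one 20% allowance to two different problems and corrects for both in a way that is valid only for missing outcomes. Either failure is not accounted for or it does not belong in the column, so the column needs correcting or explaining.

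The size of any shortfall depends on an unstated split. Across the bold malaria rows, power is about 0.88–0.89 with 5 points of failure, 0.86–0.88 with 10, and 0.81–0.84 with all 20. This assumes that failures are retained, keep roughly the control risk, and are not already reflected in P1. A partly effective course would dilute the effect less.

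The figures are for one comparison of two independent proportions. They ignore household clustering and the repeated smears, so they measure the effect of this one step and are not the trial's actual power.

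**What to change.** - Give separate rates for loss to follow-up and for treatment failure, and define treatment failure for this purpose.
- Divide N by (1 − loss) only. Carry failure through the predicted prevalence, P1* = P1 + f(P0 − P1), and recompute N at P1*, not with the approximate 1/(1 − f)² factor.
- If P1 is already net of failures, say so and remove failure from the column header.
- State that failures are analysed in the arm to which they were randomised.
- Restate the malaria totals or, where enrolment is already fixed, the power achieved at that number.

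The cost is a recalculated table and, unless P1 is already net of failures, a slightly less favourable stated power. Trial conduct does not change.
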